### Screening assessments

*Development and Wellbeing Assessment (DAWBA):* The
DAWBA will be used to collect information on the child’s behavioural adjustment and mental health. The DAWBA has been used both in UK national and international surveys
^25–
28^. The DAWBA data will be reviewed by a psychiatrist in accordance with the ICD-10/DSM-V diagnostic criteria. This methodology has been used successfully to gather data of high quality by parental online report. The DAWBA autism module includes a social aptitude scale (SAS) which measures social understanding and social ability (Liddle
*et al*., 2009). Participants displaying significant difficulties in the SAS will be eligible for the intervention. The DAWBA is available in 26 languages. The DAWBA will be completed online by parents.

*Strengths and Difficulties Questionnaire (SDQ):* The
SDQ is a brief behavioural screening questionnaire
^29^. The SDQ includes scales that measure emotional symptoms, conduct problems, hyperactivity/inattention difficulties, peer relationship problems and prosocial behaviour. The first four scales are combined to create a total difficulties score. An additional impact scale measures the impact of this composite score on daily life. Participants scoring poorly on the peer relationships subscale will be eligible for the intervention. It has been validated for use in children aged 4–17 in UK National studies of psychological adjustment, and a new form for 18+ years old has recently been developed. It will be completed online by the adolescents, parents and teachers.

*Social Responsiveness Scale (SRS):* The SRS measures the severity of autistic traits and the instrument has convergent validity with other ASD diagnostic tools
^30,
31^. The SRS subscales measure Social Awareness, Social Cognition, Social Communication, Social Motivation, and Restricted Interests and Repetitive Behaviour. The SRS will be administered online to parents and teachers.

*Health Questionnaire (HQ):* The questionnaire was developed by the UCLH Turner Syndrome Life Course Project to record information about physical health, health care, education, social life, physical activity and relationships
^32^. The self-report version of the questionnaire will be completed by adolescents. 

*Schedules for the Assessment of Social Intelligence (SASI):* The SASI is a socio-cognitive assessment that measures facial expression recognition, face recognition memory, gaze-monitoring and theory of mind. The SASI is sensitive to subtle deficits in social cognition and has been shown to have excellent reliability and validity
^33^. Adolescents will be asked to complete the SASI online.

*Wechsler Adult Intelligence Scale - Fourth UK Edition (WAIS-IV UK):* The WAIS-IV is an IQ test which measures verbal comprehension, perceptual reasoning, working memory and processing speed. It has been widely used and validated
^34^. It will be administered to adolescents in person.

*PEERS Screener:* The PEERS Screener Questionnaire assesses the participant’s motivation to take part in the PEERS intervention
^18^. It will be administered to parents and adolescents over the phone or in person. Only participants motivated to take part will be considered for the intervention.

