### Participant inclusion and exclusion criteria

Inclusion criteria for the intervention include: 1, a confirmed diagnosis of TS (monosomy, variant, mosaic etc.); 2, age 16–20 years; 3, significant social skills difficulties as screened for in the SOAR online questionnaires (see screening assessment measures section for details) and clinical judgement; 4, motivation to take part.

The exclusion criteria for the intervention include: 1, profound hearing or vision impairments (eg. complete deafness or blindness); 2, intellectual disability (VIQ<70); 3, concurrent participation in other psychological treatment.

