### Assessments

Participants will complete assessments at different time points throughout the study. The study will last 9 months in total, including a 3 month baseline, 2 months of intervention and a 3 month follow-up period. The screening measures will be delivered at T=0, the baseline assessments will be delivered at T=12 weeks and the post intervention assessments will be delivered at T=20 weeks. The primary outcome measure will be delivered at regular intervals of 4 weeks throughout the course of the study (see
Table 1).

**Table 1. T1:** Assessment timeline. Informants for each assessment are included in brackets (P – Parent; T – Teacher; YP – Young Person). Assessment acronyms: BAI – Beck’s Anxiety Inventory; IAQ – Intervention Acceptability Questionnaire; PEERS – Program for Education and Enrichment of Relational Skills; PEERS QSQ – PEERS Quality of Socialisation Questionnaire; PEERS TASSK – PEERS Test of Adolescent Social Skills Knowledge; RSE – Rosenberg Self-esteem Scale; SCP – Social Competence with Peers; SDQ – Strengths and Difficulties Questionnaire; SRS – Social Responsiveness Scale; SASI - Schedules for the Assessment of Social Intelligence; SWS – Spence Social Worries Scale; WAIS-Wechsler Adult Intelligence Scale.

Timeline	Assessments
t=0	SCP (P) 1 PEERS Screener (P,YP) SASI (YP) WAIS (YP)
4 weeks	SCP (P) 2
8 weeks	SCP (P) 3
**Baseline** 12 weeks	SCP (P,YP,T) 4 SWS (P,YP,T) PEERS QSQ (P) PEERS TASSK (YP) RSE (YP) BAI (YP) SRS (P,T) SDQ (P,T)
16 weeks	SCP (P) 5
**Post-intervention** 20 weeks	SCP (P) 6 SWS (P,YP,T) PEERS QSQ (P) PEERS TASSK (YP) RSE (YP) BAI (YP) SRS (P,T) SDQ (P,YP,T) IAQ (P,YP) SASI (YP)
24 weeks	SCP (P) 7
28 weeks	SCP (P) 8
**Follow-up** 32 weeks	SCP (P,YP,T) 9

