### Secondary outcome measures

*Strengths and Difficulties Questionnaire (SDQ):* Described previously. It will be completed by the young people, parents and teachers at baseline and post-intervention.

*Social Responsiveness Scale (SRS):* Described previously. It will be completed online by parents and teachers at baseline and post-intervention.

*Spence Social Worries Scale (SWS):* The Spence Social Worries Scale is a psychological questionnaire designed to identify symptoms of social phobia and other forms of anxiety, in children and adolescents. The parent and teacher forms are reported to have excellent internal validity
^35^. It will be completed online by the adolescents, parents and teachers at baseline and post-intervention.

*Schedules for the Assessment of Social Intelligence (SASI):* Described previously. It will be administered online to the adolescent at baseline and post-intervention.

*PEERS Test of Adolescent Social Skills Knowledge (TASSK):* The TASSK is a questionnaire designed to evaluate what the participants have learned from the intervention
^18^. This is the only outcome measure to evaluate changes in social knowledge. It will be administered to the adolescents at baseline and post-intervention.

*PEERS Quality of Socialisation Questionnaire (QSQ):* The QSQ is designed to evaluate the quality of young people’s socialization and frequency of get-togethers
^18^. It will completed online by the parents at baseline and post-intervention.

*Rosenberg Self-esteem Scale (RSE):* The RSE scale is assesses global self-esteem
^36^. It will completed online by the adolescent at baseline and post-intervention.

*Beck’s Anxiety Inventory (BAI):* This scale is a self-report measure used for measuring the severity of anxiety in children and adults
^37^. It will be completed online by the parent and adolescent groups at baseline and post-intervention.

*Camouflaging measure (CAT-Q):* The CAT-Q measures camouflaging (e.g. strategies to mask or compensate autistic characteristics) behaviour in social situations. It is comprised of 25 items and has high internal reliability in autistic adults. Its subscales measure compensation, masking and assimilation
^38^. The CAT-Q will be completed by adolescents.

*Intervention Acceptability Questionnaire (IAQ):* The IAQ has been developed for the study to assess parent and adolescent satisfaction with the intervention (

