### Statistical analysis

The primary outcome measure (SCP questionnaire)
^16^ will be analysed using visual analysis and multi-level modelling to track individual participant changes over 9 months from baseline to follow up
^39^.

The secondary outcome measures will be analysed for pre-post differences. Data will be analysed using SPSS version 22 statistical software. It is likely that we will be underpowered to detect any significant statistical differences between the pre and post intervention scores; therefore effect sizes (Cohen’s d) will also be calculated. The parent, teacher and adolescent responses to the questionnaires will also be compared to investigate the consistencies between different informants.

We anticipate that adolescent informants will report the greatest positive changes compared to other informants. We also anticipate that the adolescents will report greater improvements on the social knowledge on the TASSK, than on the social performance on the SCP or SDQ (prosocial or peer scale) and social cognition on the SASI. We also expect to see secondary improvements on adolescent self-reports of anxiety on the BAI raw score, social anxiety on the SWS raw total score and self-esteem on the RSE raw total score. We expect to see an increase in camouflaging on the CAT-Q on all the subscales.

In line with previous social skills intervention research we anticipate that positive changes in social performance will be noted by the parents, but that schoolteachers will not observe a change post intervention on the SRS, SDQ and SWS. Specifically we expect parents to report improvements in the SWS total raw score, as well as improvements on the SDQ raw prosocial scale and peer difficulties scale, and improvements on the SRS social communication scale and repetitive and ritualised behaviours scale.

The acceptability of the intervention to families will be assessed using the IAQ. Descriptive statistics will be used to summarise the responses alongside a qualitative summary of the open text answers. We expect that most families will report having positive experiences of the PEERS programme. Based on previous randomised controlled trials we predict that adherence will be on average 80% and that up to two participating families may dropout (Laugeson
*et al.,* 2015; Schohl
*et al.,* 2014).

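### The SDQ peer scale is both a route into the trial and an outcome, yet the plan shows no untreated change for the SDQ or SRS, and Table 1 leaves the young person's pre-treatment SDQ unclear

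*Protocol article*

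**What the plan says.** **Selection.** Under Participant inclusion and exclusion criteria, entry requires "significant social skills difficulties as screened for in the SOAR online questionnaires", together with clinical judgement. Screening assessments gives two routes. For the SDQ, "Participants scoring poorly on the peer relationships subscale will be eligible for the intervention". For the social aptitude scale of the DAWBA, "Participants displaying significant difficulties in the SAS will be eligible for the intervention". The SRS is listed among the screening measures but is not named as an eligibility criterion.

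**Outcome.** Under Statistical analysis, parents are expected to report "improvements on the SDQ raw prosocial scale and peer difficulties scale". A gain is also predicted for two parent-rated SRS subscales, social communication and repetitive behaviours. The method is brief: "The secondary outcome measures will be analysed for pre-post differences", with Cohen's d. The design is uncontrolled.

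**Timing.** The Assessments section says "The screening measures will be delivered at T=0", with baseline at week 12 and post-intervention at week 20. Screening assessments has the SDQ completed by young person, parent and teacher, and the SRS by parent and teacher. For the SDQ as an outcome, Secondary outcome measures says: "It will be completed by the young people, parents and teachers at baseline and post-intervention". Table 1 differs. Its t=0 row has neither SDQ nor SRS, its week-12 row has the SDQ from parent and teacher only, and its week-20 row has the SDQ from all three informants.

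Only the parent-rated SCP, the primary outcome, has repeated untreated scores (weeks 0, 4, 8 and 12).

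**The concern.** When people enter a study partly because they scored badly on a scale, their next score on it tends to be better without any treatment. With no control group, the only protection is a pre-treatment score taken after selection, or a view of how scores moved before treatment began. The SCP has both. The SDQ and SRS have the first for parents and teachers and the second for nobody, although the screening forms could supply it.

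The young person's SDQ is the weak spot. Statistical analysis compares adolescents' gains on the TASSK with their gains on the SDQ prosocial or peer scale, and expects adolescents to report larger gains than other informants. If the young person's change ran from screening to week 20 while parents' and teachers' changes ran from week 12 to week 20, the informants would be compared over different intervals, and possibly with a selection effect in only one of them.

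**Working it through.** **1. What the plan provides as a pre-treatment score**

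| Measure, informant | Screening (text) | t=0 (Table 1) | Week 12 (text) | Week 12 (Table 1) | Week 20 (Table 1) |
|---|---|---|---|---|---|
| SDQ, parent and teacher | yes | no | yes | yes | yes |
| SDQ, young person | yes | no | yes | **no** | yes |
| SRS, parent and teacher | yes | no | yes | yes | yes |

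The SASI shows why the word baseline does not settle the matter. Secondary outcome measures places it at baseline and post-intervention, but Table 1 has it at t=0 and week 20 only. There, baseline means the screening occasion.

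**2. Inputs for the size of the effect**

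The article gives no SDQ cut-off, retest correlation or SD, and no stated figure exists to reproduce. The following are assumptions: the worst 10 to 30% on the scale are selected; the retest correlation r is 0.6 to 0.8; slow fluctuations in score decay with a time constant of 8 to 26 weeks. Treatment effect is set to zero.

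**3. Change measured from the selecting score**

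Expected apparent improvement = (1 − r) × i, where i is the mean depth of selection in SD units (normal density at the cut-off divided by the share selected).

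- Worst 10%, r = 0.6: 0.4 × 1.75 = 0.70 SD
- Worst 20%, r = 0.7: 0.3 × 1.40 = 0.42 SD
- Worst 30%, r = 0.8: 0.2 × 1.16 = 0.23 SD

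**4. Change measured from the separate week-12 score**

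Expected apparent improvement = (correlation of weeks 0 and 12 − correlation of weeks 0 and 20) × i, here with the worst 20% selected (i = 1.40).

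- Independent errors: (0.70 − 0.70) × 1.40 = 0 SD
- 50% stable trait, 30% fluctuating state, 20% error, time constant 8 weeks: correlations 0.57 and 0.52, giving 0.06 SD
- 50% trait, 50% state, time constant 16 weeks: correlations 0.74 and 0.64, giving 0.13 SD

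(The last two results were computed from unrounded correlations.)

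**5. Scale against the precision of the study**

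The standard error of a mean change is about √(2(1 − r)/n). With r = 0.8 and n = 10 it is √(0.4/10) = 0.20 SD; with r = 0.6 and n = 6 it is √(0.8/6) = 0.37 SD. Even the largest residual in step 4 is smaller than one standard error (0.13/0.20 = 0.65). The step 3 figures range from about 0.6 of a standard error (0.23/0.37) to 3.5 (0.70/0.20), depending on how the assumptions combine.

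**The case against.** The strongest reply is that the design already deals with the problem. Screening and baseline are separate occasions, the SDQ and SRS are measured afresh at week 12, and what remains is small beside the sampling error of 6 to 10 girls in a study that calls itself likely underpowered. These are secondary outcomes in an openly uncontrolled pilot. The primary outcome has four untreated parent scores. The Sample size section does not say that the SDQ or SRS will size the future trial. All of this stands and limits the point.

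A reader might infer four stronger things, none of which the document supports.

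- *That the predicted parent gains are biased by 0.2 to 0.7 SD.* That size applies only to change measured from the selecting score. For parents and teachers, both the text and Table 1 give a week-12 form.
- *That the SRS has the same selection problem.* It is not a named eligibility measure. The SDQ peer scale is itself only one route, so depth of selection on it is uncertain.
- *That treated change should count as improvement only if it exceeds the earlier untreated change.* For the SDQ peer scale, the first interval contains nearly all the regression to the mean, so the rule would be biased against the intervention. The intervals also differ (12 weeks against 8, if screening is at t=0). They share the week-12 score, so with independent errors the contrast has √(6/2) = 1.7 times the standard error of the simple change.
- *That screening scores are available for every participant.* They come from SOAR, a larger study from which girls are later invited. Their absence from the t=0 row may mean that they were completed earlier, and complete teacher returns are not documented.

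Nor does the article say that a screening score may replace a missing week-12 score. A rule on that can properly sit in an analysis plan, so its absence is not a fault here.

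**Conclusion.** The point holds as a cheap improvement to the secondary analyses and a correction to the schedule. It is not evidence that the planned parent and teacher comparisons are seriously biased. For those informants the residual selection effect is about 0 to 0.13 SD, and the real gap is that untreated change on the SDQ and SRS is not shown. For the young person's SDQ, the text and Table 1 disagree on whether a week-12 score exists. If Table 1 is right and the young person's own screening score was the one used to select, about 0.2 to 0.7 SD of improvement could appear without any treatment effect. All these sizes rest on assumed reliability, selection depth and decay of fluctuations.

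**What to change.** 1. Reconcile Table 1 with the Assessments, Screening assessments and Secondary outcome measures sections. Show the screening SDQ and SRS at the time they are actually completed, and settle whether the young person completes the SDQ at week 12.
2. State that week 12 is the pre-treatment value for the SDQ and SRS, for every informant who reports them.
3. For each informant, report the dated screening-to-week-12 change beside the week-12-to-week-20 change, with the length of each interval. Present this descriptively, without a test and without making one change a threshold for the other.
4. Note beside the table that the first-interval change on the SDQ peer scale includes regression to the mean, and that the SRS is the cleaner comparison because it is not a named selection measure.

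**Cost.** One extra column in the secondary-outcome table and a corrected Table 1. If the young person's week-12 SDQ is not currently planned, one additional brief questionnaire at an existing assessment. **Downside.** Screening dates, and so interval lengths, may vary between girls, and some screening forms may be missing, so the untreated column will be a rough guide only.

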### Primary outcome measures

*Social Competence with Peers (SCP):* The SCP assesses the consequences of young people’s interactions with peers, such as the existence and duration of friendships or social invitations
^35^. A modified version of the SCP will be used to adapt the tool for use in young adults. The adolescent group and the parent group will be asked to complete the SCP at regular intervals (every 4 weeks) from baseline to follow-up. Teachers will be asked to complete the SCP at baseline, post-intervention and follow-up.

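### Text and Table 1 contradict each other on who completes the primary outcome (SCP): if Table 1 is followed, no adolescent or teacher SCP score exists at week 20

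*Protocol article*

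**What the plan says.** The section headed Primary outcome measures sets the SCP schedule by informant. For adolescents and parents: "The adolescent group and the parent group will be asked to complete the SCP at regular intervals (every 4 weeks) from baseline to follow-up". For teachers: "Teachers will be asked to complete the SCP at baseline, post-intervention and follow-up".

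The Assessments section fixes the end-of-treatment point: "the post intervention assessments will be delivered at T=20 weeks". It also says that the primary outcome is repeated every 4 weeks, without naming informants. Table 1 in that section then lists informants visit by visit (P parent, YP young person, T teacher). The week 12 row begins "SCP (P,YP,T) 4 SWS (P,YP,T) PEERS QSQ (P" and the week 20 row begins "SCP (P) 6 SWS (P,YP,T) PEERS QSQ (P" (both quotes are cut inside the last bracket). Week 32 again shows P, YP and T for the SCP. Every other row shows P alone.

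The Statistical analysis section relies on adolescent SCP change. It predicts that adolescents will report "greater improvements on the social knowledge on the TASSK, than on the social performance on the SCP", with two SDQ scales and the SASI as further comparators. It also states: "We anticipate that adolescent informants will report the greatest positive changes compared to other informants", and plans to compare parent, teacher and adolescent responses.

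**The concern.** The text and the table cannot both be carried out, and the conflict falls on the primary outcome at the end of treatment. Study staff usually work from the schedule table. If they do so here, adolescents and teachers are not asked for the SCP at week 20, and a rating of how things stood at that time cannot be collected afterwards.

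Two planned uses of the data would suffer. The TASSK is given only at weeks 12 and 20, so a like-for-like contrast with the adolescent SCP needs a week 20 SCP score. A comparison of the three informants on the primary outcome at the end of treatment needs all three of them at that visit. Teachers matter here because they are the one informant group that does not take part in the programme, and the Discussion itself warns of expectancy bias in adolescent and parent reports.

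**Working it through.** There is no sample size or power figure to reproduce. The check is a count of SCP occasions under each schedule.

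**Inputs.** The text schedule is from Primary outcome measures, the table schedule is from Table 1, and the group size of 6 to 10 is from Sample size.

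| Week | Table 1 | Text, with baseline read as week 12 |
|---|---|---|
| 0, 4, 8 | P | not specified |
| 12 | P, YP, T | P, YP, T |
| 16 | P | P, YP |
| 20 | P | P, YP, T |
| 24, 28 | P | P, YP |
| 32 | P, YP, T | P, YP, T |

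**Adolescents.** Occasions under the text = (last week − first week) / 4 + 1.
- Baseline read as week 12: (32 − 12) / 4 + 1 = 6.
- Baseline read as the whole baseline phase from week 0: (32 − 0) / 4 + 1 = 9.
- Table 1: 2 (weeks 12 and 32).
- Shortfall per adolescent: 6 − 2 = 4, or 9 − 2 = 7 on the wider reading.

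**Teachers.** Text: 3 (weeks 12, 20 and 32). Table 1: 2 (weeks 12 and 32). Shortfall: 1, at week 20.

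**Parents.** Table 1 gives 9, numbered 1 to 9 without a gap.

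**Week 20 alone.** With 6 to 10 families, the text calls for 6 to 10 adolescent and 6 to 10 teacher SCP forms. Table 1 calls for none of either.

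**Effect on the TASSK contrast.** TASSK change spans 20 − 12 = 8 weeks. The only adolescent SCP change available under Table 1 spans 32 − 12 = 20 weeks, which combines any immediate gain with what is kept or lost over the following 12 weeks. A difference between the two changes could then reflect timing as well as the knowledge-versus-performance distinction it is meant to show.

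**Do the other comparators fill the gap?** Not as Table 1 stands. It lists the SDQ for parent and teacher at week 12 and adds the young person only at week 20, so the adolescent SDQ has no week 12 score either. A screening SDQ may exist, but it is not the week 12 baseline. The SASI appears at weeks 0 and 20, so its change also covers a different period from that of the TASSK.

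**Is the table simply garbled?** The numbering and informant codes are intact. The same week 20 row lists YP and T for the SWS and the SDQ, so the table expects both informants at that visit and omits them from the SCP only.

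**The case against.** The strongest reply is that the loss is conditional. If staff follow the text, every score exists, and the article does not say which schedule governs. A reader might infer that adolescent and teacher change on the primary outcome cannot be computed at all. The documents do not support that: even under Table 1, a week 12 to 32 change is available for all three informants.

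A reader might also infer that the primary analysis fails because two points cannot carry a trajectory. That does not follow. The Statistical analysis section plans visual analysis and multi-level modelling of the SCP without saying that an adolescent or teacher series will be modelled. The parent series has 9 points, and the Discussion assigns maintenance to the parent report. The effect size for a later trial can still come from the parents.

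Nor is a stated teacher hypothesis lost. The teacher prediction names the SRS, SDQ and SWS, all of which Table 1 collects from teachers at weeks 12 and 20. The general statement about adolescents changing most names no instrument, and the SWS allows a three-informant comparison at both visits. The Discussion is itself unclear about teachers: it gives them as an example of external observers and then says that such assessment is not feasible.

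Finally, this is a feasibility and acceptability pilot that already expects to be underpowered.

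All of this stands, and it limits the consequence. It does not remove the contradiction, nor the mismatch in the one prediction that names the adolescent SCP.

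**Conclusion.** The concern holds as an internal inconsistency about who completes the primary outcome. If Table 1 is followed, adolescents have 2 SCP scores against at least 6 under the text, teachers have 2 against 3, and neither informant has a week 12 to 20 change. The adolescent TASSK-versus-SCP contrast would then compare 8 weeks with 20, and an end-of-treatment comparison of informants on the SCP would not be possible.

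This rests on two assumptions: that Table 1 is the schedule used, and that post-intervention means week 20, as the Assessments section states. The count of 6 also takes baseline as week 12; it becomes 9 if baseline means the phase from week 0. The parent series and its planned analysis are unaffected.

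It should be fixed, because missed ratings cannot be recovered and the correction is small. It does not undermine the main aims of piloting the programme and assessing its feasibility and acceptability.

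**What to change.** - Reconcile Primary outcome measures with Table 1 by stating, for each time point, which informants complete the SCP.
- Change the week 20 entry in Table 1 to SCP (P,YP,T). Both added informants already complete other forms at that visit.
- For the remaining 4-weekly points from baseline to follow-up (weeks 16, 24 and 28, and weeks 0, 4 and 8 if baseline means the whole phase), either add YP to Table 1 or amend the text so that only parents complete the 4-weekly series.

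The cost is one more short form for each adolescent and each teacher at week 20, that is 6 to 10 of each. Restoring the full adolescent series adds 3 more forms per adolescent on the week 12 reading (6 − 2 − 1) or 6 more on the week 0 reading (9 − 2 − 1). That extra burden is the reason to consider the parent-only option at those points.
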